## Abstract

**Background:**

A few recent studies have found indications of the effectiveness of inpatient psychotherapy for depression, usually of an extended duration. However, there is a lack of controlled studies in this area and to date no study of adequate quality on brief psychodynamic psychotherapy for depression during short inpatient stay exists. The present article describes the protocol of a study that will examine the relative efficacy, the cost-effectiveness and the cost-utility of adding an Inpatient Brief Psychodynamic Psychotherapy to pharmacotherapy and treatment-as-usual for inpatients with unipolar depression.

**Methods/Design:**

The study is a one-month randomized controlled trial with a two parallel group design and a 12-month naturalistic follow-up. A sample of 130 consecutive adult inpatients with unipolar depression and Montgomery-Asberg Depression Rating Scale score over 18 will be recruited. The study is carried out in the university hospital section for mood disorders in Lausanne, Switzerland. Patients are assessed upon admission, and at 1-, 3- and 12- month follow-ups. Inpatient therapy is a manualized brief intervention, combining the virtues of inpatient setting and of time-limited dynamic therapies (focal orientation, fixed duration, resource-oriented interventions). Treatment-as-usual represents the best level of practice for a minimal treatment condition usually proposed to inpatients. Final analyses will follow an intention–to-treat strategy. Depressive symptomatology is the primary outcome and secondary outcome includes measures of psychiatric symptomatology, psychosocial role functioning, and psychodynamic-emotional functioning. The mediating role of the therapeutic alliance is also examined. Allocation to treatment groups uses a stratified block randomization method with permuted block. To guarantee allocation concealment, randomization is done by an independent researcher.

**Discussion:**

Despite the large number of studies on treatment of depression, there is a clear lack of controlled research in inpatient psychotherapy during the acute phase of a major depressive episode. Research on brief therapy is important to take into account current short lengths of stay in psychiatry. The current study has the potential to scientifically inform appropriate inpatient treatment. This study is the first to address the issue of the economic evaluation of inpatient psychotherapy.

**Trial registration:**

Australian New Zealand Clinical Trial Registry (ACTRN12612000909820)

## Background

Depression is the largest contributor to the burden of disease in high-income countries, with further increase expected [1]. Depression may not respond to outpatient treatment and may be so severe that hospital stay may be needed [2,3]. Patients with severe symptoms benefit more from acute inpatient treatment than from day-hospital care [4]. Symptom improvement during first inpatient treatment is a significant predictor of the cumulative length of inpatient stay and the number of inpatient episodes over five years [5]. Those results are consistent with more recent literature that recommends an intensive inpatient acute treatment of depression [3,6].

Due to the shift of locus of mental health care in most Western countries towards outpatient care, research on role and content of acute intensive inpatient psychiatric care have received limited attention [7]. The vast majority of depressed inpatients receive pharmacotherapy, but receive psychotherapy less frequently [8-10]. Several meta-analyses support the advantage of combining pharmacotherapy and psychotherapy to treat outpatients with severe or complex depressive disorders [11-15]. The only review of combined therapy for depressed inpatients concluded that combined treatment appeared advantageous in therapy-resistant, chronic and severe forms of depressive disorders [16]. Its generalizability is limited by relatively small sample sizes and heterogeneity in diagnosis of depression, though. The best well-controlled study available in this field of research compared interpersonal psychotherapy and pharmacotherapy vs. pharmacotherapy and clinical management for 124 inpatients with major depressive disorder. This randomized controlled trial showed that inpatient depression-specific psychotherapy augmented pharmacotherapy [6].

Meta-analysis and mega-analysis findings support the efficacy of brief psychodynamic therapy for outpatient with depression [17-19]. While yet unsufficient, research on efficacy and effectiveness of psychodynamic psychotherapy as a inpatient treatment of depression gives some indications to foster examination of its validity. In a review of 9 German studies, inpatient psychotherapy, mostly psychodynamic, demonstrated good efficacy (average effect size, d = 0.84). Depression and obsessive-compulsive disorders showed the best results, but usually for psychotherapies of longer duration [20]. One cohort study on a sample of 83 consecutive inpatients examined the outcomes of short-term psychodynamic inpatient psychotherapy. Over the course of the 4 weeks of treatment, distress returned to normal range for 64% of patients and remained stable one year later [21]. This study had two major limitations. It was a complete analysis and it did not compare the treatment to a valid comparator. Based on a randomized control trial with a two parallel group design, one study explored the efficacy of an interpersonal brief (5 weeks) and intensive (15 individual and 8 group sessions) psychotherapy program combined with pharmacotherapy compared to medication and clinical management. Response rate (70% vs 51%) and remission rate (49% vs. 34%) were higher for psychotherapeutic group at discharge; after the three-month follow-up the relapse rate (3% vs. 25%) also favored the psychotherapeutic group; finally between treatment effect sizes evolved from moderate (at discharge) to large during the follow-up period (3 and 12 months) [6]. Results for a subsample of 45 patients with chronic depression revealed also a significantly greater reduction of depressive symptoms, as well as better global functioning [6,22].

Little systematic research has been conducted into the ideal dosage of brief psychotherapy. Evidence come from the outpatient setting. Between 12 and 18 sessions of therapy are required for 50% of patients to improve, according to a clinical significance perspective [23]. The Second Sheffield Psychotherapy Project found that 16 sessions were significantly more effective than 8 sessions for patients with severe depression [24]. The nature of the change aimed at should be taken into account, however [23]. Recovery from maladaptive interpersonal patterns, for example, typically requires higher doses of psychotherapy than does recovery from symptoms of depression or broader distress [25]. Changes at four weeks of inpatient psychotherapy are equivalent to a one-year follow-up for psychological distress but not for interpersonal problems [6,26].

Inpatient psychiatric treatment has been under great economic pressure to cut costs with the result of decrease in length of stay [27,28]. The brevity of inpatient stay has lead to discard psychotherapy and hindered examination of its potential cost-effectiveness. Research in outpatient care has found that although the cost of combination therapy in the initial treatment is substantially higher, these costs are in part offset by lower subsequent treatment costs [29-31]. Improvement during the acute phase of treatment is important because it is associated with lower subsequent costs across the full range of mental health and general medical services [32]. Currently there is no study done on the economicity of inpatient psychotherapy for depression.

In summary, current state of research support the need for well-controlled trials to examine the effectiveness and cost-effectiveness of inpatient acute treatment of depression, including adjunctive brief dynamic therapy to augment pharmacological treatment.

### Objectives

The first purpose of the study is to estimate the relative efficacy of combined inpatient brief psychodynamic psychotherapy (IBPP) and pharmacotherapy compared to medication and clinical management on short- and long-term outcomes of inpatients with severe, recurrent or chronic depression (including so-called treatment-resistant) according to the DSM-IVTR. The second objective is to study the cost-effectiveness and the cost-utility of the IBPP. The third objective is to document the specific and the combined influence of the therapeutic alliance with the individual psychotherapist and with the clinical team as mediators of patient’s change.

## Methods/Design

### Study design

This trial is registered as: “Efficacy of an adjunctive brief psychodynamic psychotherapy compared to treatment-as-usual for psychiatric inpatients with unipolar major depressive episode” at the Australian New Zealand Clinical Trial Registy (ACTRN12612000909820). It has been peer-reviewed in the successful funding selection process by the Swiss National Science Foundation (Grant 32003B_135098/1). This protocol proposes a one month randomized controlled trial (RCT) with a 12-month naturalistic follow-up. Figure 1 illustrates the two parallel group design where patients included in the study are randomized either to (1) the intervention group (adjunctive short-term dynamic psychotherapy, IBPP), or to (2) the control treatment group, which represents the best level of practice for a minimal treatment condition usually applied to hospitalized patients (treatment-as-usual, TAU). After the one month period, patients will be referred to continuation treatment as usual.

**Figure 1 F1:**
[figure not shown]
Flow chart of the research plan.

### Ethics approval

Ethics approval was granted by the Ethics Committee of the University of Lausanne (12/04/2010).

### Inclusion and exclusion criteria

All patients admitted in the university psychiatric hospital section specialized for the treatment of mood, anxiety and personality disorders are eligible to participate in the study if they meet the following inclusion criteria: (1) Age 18–65 years old; (2) unipolar major depressive episode; (3) Montgomery-Asberg Depression Rating Scale > 18; (4) sufficient mastery of the French language.

Exclusion criteria are: (1) Any organic medical disorder, or persistent substance use/dependence which might affect brain function (memory, level of consciousness, cognitive abilities) thereby impairing the individual from participating and benefiting from psychotherapy; (2) A psychotic disorder which makes a pronounced break in reality testing chronically or intermittently likely, such as schizophrenia, delusional disorder, or bipolar manic-depression (Type I); (3) Any of the following which are considered unlikely to benefit from either treatment: axis II paranoid, schizoid or schizotypal, and borderline personality disorder, which are considered either contraindicated for some treatments, or unlikely to respond [33]; antisocial personality characterized by frequent lying, lack of guilt or remorse or history of volatile aggressiveness or violence; recent suicide attempts necessitating residential or day treatment and acute risk for suicide; other principal axis I disorder; severe cognitive impairment; previous absence of response to the study treatments.

### Power calculation

Based on previous studies, at least moderate effect sizes of psychodynamic psychotherapy on patient outcome (e.g. f = .25 for severity of depressive symptomatology) could be expected. Power analysis (with two-tailed alpha set at .05 and a power of .80) for repeated measure ANOVA indicates that 108 patients (54 in each group) are sufficient to detect the expected effects [34]. With 22% of non-completers, an *intent-to-treat sample* of 138 patients (69 in each group) is required in order to have a *completer sample* of 108 patients. All analysis will be done on the two samples.

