#### Psychopathology

##### Depression

Depressive symptoms are the primary outcome. This is assessed by two instruments: (1) The Montgomery-Asberg Depression Scale (MADRS; [39]), a clinician rating measure in 10 items, which serves as our primary outcome measure, and (2) the self-rated version of the Inventory of Depressive Symptom (QIDS-SR_16_; [40]), a 16-item self-report measure of depressive symptoms. To allow for Kaplan-Meyer estimates of speed of response, MADRS is done on a weekly basis. The Depressive Experience Questionnaire (DEQ; Blatt SJ, D’Afflitti J, Quinlan DM: Depressive Experiences Questionnaire, Unpublished research manual, Yale University; 1979) assesses a wide range of life experiences often reported by depressed individuals but not considered symptoms of depression. Its well-established factor structure measures two primary dimensions: interpersonal relatedness and self definition.

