### Data analysis

Final analyses will follow an intention-to-treat strategy comparing patients in the groups to which they were originally randomized. Clinical Significance method will be used to estimate rates of response (reliable improvement), remission (clinical significance), recovery (maintained clinical significance) and relapse (deterioration) [63]. For short-term outcome, repeated-measure analyses of variance (ANOVA) and analyses of covariance (ANCOVA - controlling for pretreatment scores and patient’s age) will be used on all outcome measures. For long-term outcome, linear mixed-effects models will be preferred, as well as for therapist and alliance effects on outcome [64]. Last Observation Carried Forward (LOCF) will be used for missing data when appropriate. Latent class analysis (using Latent Gold 4.5) will be done to explore the effect of moderating variables.

Cost-effectiveness analysis will be done in collaboration with the Institute of Health Economics and Management (IHEM) of the University of Lausanne. An economist at the IHEM will be in charge of the data analysis. The economic evaluation will be conducted from the perspective of the health system. Primary outcome will be remission in depressive symptomatology at 12 months. The comprehensively measured service costs between the two treatments will be compared with the difference in change in the primary outcome measure and with the difference between the treatments in QALYs gained.

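### The sample size rests on a repeated-measures ANOVA whose powered effect is not named, and the short-term plan runs that ANOVA beside an ANCOVA with no rule for which decides

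*Protocol article*

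**What the plan says.** The Power calculation section of the protocol article expects moderate effects ("e.g. f = .25 for severity of depressive symptomatology) could be expected"), sets the error rates ("with two-tailed alpha set at .05 and a power of .80"), and concludes that a power analysis "for repeated measure ANOVA indicates that 108 patients (54 in each group) are sufficient to detect the expected effects". It then allows for 22% non-completion, which gives 138 randomised, and says that every analysis will be run on both the intention-to-treat and the completer samples.

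The Data analysis section says that, for the short term, "repeated-measure analyses of variance (ANOVA) and analyses of covariance (ANCOVA - controlling for pretreatment scores and patient’s age) will be used" on all outcome measures. Mixed models are kept for the long term. The same section and the abstract say that final analyses follow intention to treat.

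The MADRS is described under Depression as "a clinician rating measure in 10 items, which serves as our primary outcome measure", and it is also rated weekly. The full battery follows this schedule: "Patients are assessed upon admission, and at 1-, 3- and 12- month follow-ups". The section on the data collection site puts the post-treatment measurement at one month.

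**The concern.** A two-group repeated-measures ANOVA contains two different tests of treatment: the group main effect, which averages over occasions, and the group-by-time interaction. They need very different sample sizes and answer different questions. The section names neither, and gives neither the number of occasions nor the correlation, so 80% power cannot be tied to a particular comparison.

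This matters because the averaged effect is a poor measure of treatment if admission is one of the occasions. Randomised arms do not differ systematically at admission, so averaging dilutes a difference seen at one month.

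Separately, the Data analysis section commits to two tests of the same short-term hypothesis and does not say which one is decisive. The conclusion could then follow whichever gives the smaller p-value.

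**Working it through.** **Inputs from the protocol article.** f = 0.25 (d = 0.5 for two groups), two-sided alpha 0.05, power 0.80, N = 108 (54 per arm), 22% non-completion. **Assumed, because not stated:** number of occasions m, correlation r between occasions (compound symmetry), and equal variances.

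**1. Reproducing 108** (noncentral F).

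- Single time point: λ = f²N. At N = 108, λ = 0.0625 × 108 = 6.75 and power is 0.73; 128 patients are needed. So 108 is not a plain one-month comparison.
- Averaged group effect: λ = f²Nm / (1 + (m − 1)r), df 1 and N − 2. With m = 2 and r = 0.68, λ = 13.5/1.68 = 8.04 and power is 0.80, so N = 108. The same N arises at m = 3, r = 0.75; m = 4, r = 0.78; and m = 5, r = 0.80. At r = 0.5 and m = 2, N is 98.
- Group-by-time: λ = f²Nm / (1 − r), df m − 1 and (N − 2)(m − 1). The largest N for m = 2 to 5 and r ≥ 0 is 66 (m = 2, r = 0); at m = 2, r = 0.5 it is 34.
- Group-by-time with f taken as already including the correlation: 128–130 at m = 2, 80–82 at m = 3, and less beyond. None is 108.
- Non-completion: 108/0.78 = 138.5, which agrees with the stated 138.

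Among these standard ANOVA formulas at f = 0.25, 108 therefore fits only the averaged group effect.

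**2. Power with 54 per arm if the true difference is d = 0.5 at one month.**

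- Averaged effect over baseline and one month, no baseline difference: the mean difference is 0.25, so λ = 0.125² × 108 × 2 / (1 + r) = 3.375/(1 + r).
- Pre-post group-by-time, which is the change-score test: λ = 0.25² × 108 / (2(1 − r)) = 3.375/(1 − r).
- Baseline-adjusted ANCOVA: λ = 0.25² × 108 / (1 − r²) = 6.75/(1 − r²). The age covariate is ignored.

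| r | Averaged, baseline included | Group-by-time | ANCOVA |
|---|---|---|---|
| 0.3 | 0.36 | 0.59 | 0.77 |
| 0.4 | 0.34 | 0.65 | 0.80 |
| 0.5 | 0.32 | 0.73 | 0.84 |
| 0.58 | 0.31 | 0.80 | 0.89 |
| 0.68 | 0.29 | 0.90 | 0.94 |

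**3. Two tests, either of which may succeed.** Simulation under no treatment effect, 69 per arm, bivariate normal baseline and one-month scores, 20,000 trials per setting. Each test alone rejects in about 5%. At least one of change-score ANOVA and ANCOVA rejects in 7.7% (r = 0.3), 7.1% (r = 0.5) and 6.8% (r = 0.68).

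**The case against.** The strongest reply is that the plan may be adequately powered as it stands. A reader might infer from step 2 that the trial has only about 30% power. The documents do not support that. It would require that the averaged effect is the one powered, that baseline counts as an occasion, and that f = 0.25 means d = 0.5 at one month only. None of these is stated. Since the MADRS is rated weekly, an average over four post-baseline ratings with r about 0.78 also gives 108, with no dilution by baseline.

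Nor does 108 belong only to the averaged effect once other tests are considered. It gives 80% power for the ANCOVA at r = 0.40 and for the pre-post group-by-time test of d = 0.5 at r about 0.58. At the r of 0.68 that reproduces 108 with two occasions, both exceed 0.80.

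A reader might also count the completer sample as a further route to success and arrive at a larger error rate. The article makes intention to treat the final analysis, so the completer results read more naturally as supportive.

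Finally, a condensed article may leave the number of occasions and the correlation to a fuller document. That is fair for those two inputs taken alone. It does not answer the rest: the article itself bases the sample size on one family of tests and commits to two tests for the short-term outcome without ordering them.

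**Conclusion.** The concern holds in limited form. The stated power is not attached to an identified effect, and the only standard repeated-measures ANOVA effect that returns 108 at f = 0.25 is the time-averaged one. If that average includes baseline, it would be a weak test of a one-month difference (power about 0.29 to 0.36). Whether the trial has 80% power for d = 0.5 at one month depends on which test decides and on the baseline correlation: group-by-time reaches it from r about 0.58, ANCOVA from r about 0.40. A power failure is therefore not shown.

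The missing rule between ANOVA and ANCOVA rests on the text alone. Its cost, if either could claim success on the intention-to-treat sample, is a type I error of about 0.07 to 0.08 instead of 0.05. The figures assume normal scores, equal variances and, in the simulation, no missing data.

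**What to change.** - In Data analysis, name one confirmatory short-term test: the treatment difference in MADRS at one month, by intention to treat, from the ANCOVA adjusted for baseline score and age that is already planned, or the equivalent one-month contrast of a mixed model. Under the step 2 assumptions it is at least as powerful as the change-score form of the ANOVA at every correlation.
- Label the repeated-measures ANOVA and the completer analyses as supportive.
- In Power calculation, restate the power for that test with its assumed baseline correlation: about 0.77 to 0.84 for 54 per arm at d = 0.5 and r = 0.3 to 0.5, and higher at larger r.

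The article reports that recruitment is closed and follow-up continues. The change therefore costs the wording of two sections, with no new patients or data, and should be fixed before the final analysis.

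### The abstract's recruitment target of 130 conflicts with the 138 the power section requires; at 130 with 22% loss the completer sample has about 77% power, not 80%

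*Protocol article*

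**What the plan says.** All references are to the protocol article.

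- **Abstract, Methods/Design:** the plan is to recruit "A sample of 130 consecutive adult inpatients with unipolar depression" who exceed the depression score threshold.
- **Power calculation:** the assumed effect is "f = .25 for severity of depressive symptomatology", the test is a repeated-measures ANOVA "with two-tailed alpha set at .05 and a power of .80", and the result is that "108 patients (54 in each group) are sufficient to detect the expected effects". The section then inflates: "With 22% of non-completers", an intent-to-treat sample "of 138 patients (69 in each group) is required" to leave 108 in the completer sample. It adds that every analysis will be run on both samples.
- **Data analysis:** "Final analyses will follow an intention-to-treat strategy comparing patients in the groups to which they were originally randomized".
- **Patients recruitment:** a dropout is a case with fewer than 5 sessions, and recruitment closed in June 2012 while follow-up continues.

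**The concern.** The abstract and the power section describe the same total and give different numbers, 130 and 138. Both are put as the plan. The abstract does not present 130 as a revised target or as the number reached. A reader of the abstract alone and a reader of the methods come away with different trials.

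The difference touches the power claim. The 138 exists only to deliver 108 completers, and .80 is attached to the 108. If 130 is the true size, the power section's own loss rate no longer delivers 108, and the 80% has no sample behind it. A non-significant result would then be judged against a power the completer analysis was not sized to have.

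A related point of labelling is that the final analyses are declared to be intention-to-treat, whereas the one power figure given refers to completers. The article should make clear which set the figure describes.

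**Working it through.** **Inputs (Power calculation unless noted).** 108 completers, 54 per arm; power .80; two-tailed alpha .05; f = .25; 22% non-completers; 138 randomised; 130 recruited (Abstract).

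**1. Reproduce the plan's inflation.** 108 / (1 − 0.22) = 108 / 0.78 = 138.5. The stated 138 agrees to rounding (138 × 0.78 = 107.6). The power section is internally consistent.

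**2. Can 130 be a variant of the same calculation?** Multiplying up instead of dividing gives 108 × 1.22 = 131.8, or 132, so that shortcut does not produce 130. The gap is 138 − 130 = 8 patients (8/138 = 5.8%), which is more than rounding.

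**3. Completers at 130.** 130 × 0.78 = 101.4, about 101, which is 7 short of 108. The loss rate at which 130 still leaves 108 is 1 − 108/130 = 16.9%. The article assumes 22%.

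**4. Completer power at 101.** The 108 cannot be rebuilt from the stated inputs, because the number of measurements and the within-patient correlation are not given. That is not counted as an error. I therefore take the plan's own statement as the anchor and choose the noncentrality that gives power 0.80 at N = 108 for an F test on 1 and 106 degrees of freedom. This is 7.99. Noncentrality scales with N:

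- N = 101: 7.99 × 101/108 = 7.47, power 0.773.

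As a check on the anchoring, specific designs that come close to 108 were also run for the between-group effect. Two measurements with correlation 0.70 give 0.770 at N = 101; three with correlation 0.75 give 0.778. The answer is 0.77 to 0.78 either way.

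In terms of detectable effect, 80% power at 101 completers needs roughly f = 0.25 × √(108/101) = 0.26 (ignoring the small change in degrees of freedom).

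**5. Intention-to-treat power, as a sensitivity calculation only.** Assume that 22% of the psychotherapy arm are non-completers and that they carry a fraction c of the effect. The average effect is then f × (0.78 + 0.22c), and the noncentrality is 7.99 × (N/108) × (0.78 + 0.22c)².

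| Effect in non-completers | Multiplier | N = 130 | N = 138 |
|---|---|---|---|
| Full (c = 1) | 1.00 | 0.87 | 0.89 |
| Half (c = 0.5) | 0.89 | 0.78 | 0.81 |
| None (c = 0) | 0.78 | 0.67 | 0.70 |

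Power is 0.80 or more as long as the average intention-to-treat effect keeps at least 91% of f = .25 at N = 130, or 88% at N = 138.

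**The case against.** The strongest reply is that the mismatch does little harm. Moving from 138 to 130 costs about 3 points of completer power, and at an undiluted f = .25 the intention-to-treat comparison has 0.87 at 130 and 0.89 at 138, above 80% at either size. Recruitment is over, so no enrolment decision hangs on it. This stands, and it makes the point a reporting correction and not a design fault. It does not remove the contradiction, since both totals are printed and nothing links them.

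A reader might go further and infer that the 80% belongs to the wrong analysis and that the intention-to-treat analysis is therefore underpowered. The article does not support this, for four reasons:

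- It openly plans both analyses. Sizing the smaller set and inflating for loss is ordinary practice.
- It takes f = .25 from previous studies and calls it at least moderate. Nothing shows that these were completer effects. If they were intention-to-treat effects, scaling by 0.78 would count dilution twice.
- The 22% is not split by arm, and a non-completer may have had up to four sessions, so no benefit at all is an extreme assumption.
- The absence of an intention-to-treat power figure is mainly an omission, of a kind a condensed article may leave to a fuller document.

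It is also fair to say that the power figures rest on a noncentrality calibrated to the stated 0.80 at 108. They should be read to two decimals at most.

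**Conclusion.** The point holds for the sample size. The article states 130 in the abstract and 138 in the power section, and under its own 22% loss 130 leaves about 101 completers with power of about 0.77, not 108 with 0.80. The counts follow directly from stated figures. The 0.77 rests on accepting the stated 0.80 at 108 and changes little across designs that come close to 108. The practical size is small, about 3 percentage points of power.

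On the analysis set, the supportable statement is narrower: .80 describes the completer sample and should be labelled so. Intention-to-treat power runs from about 0.67 to 0.87 at 130, or 0.70 to 0.89 at 138, depending on an assumption the article cannot settle. That range does not show a shortfall.

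**What to change.** 1. State one sample size in the abstract and the power section. As recruitment has closed, give the number actually randomised, and if it differs from 138, say so and why.
2. Keep the calculation of 108 completers and 138 randomised as the planning rationale. Beside it, give the power or detectable effect at the number randomised, in place of an unqualified 80%.
3. Say that .80 refers to the completer sample. Because the final analyses follow intention-to-treat, add the range in the table above for the number randomised, labelled as resting on an assumed effect in non-completers.
4. Do not enrol more patients on account of this.

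The cost is a text correction in two places and a short calculation. No analysis, estimand or procedure changes. The stated completer power may become slightly less favourable.
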